**Assessments^b^**											
	Job-search intensity and effort			✓		✓		✓		✓	
	Job-search quality			✓		✓		✓		✓	
	Job-search self-efficacy			✓		✓		✓		✓	
	Self-esteem			✓		✓					
	Inoculation against setbacks			✓		✓					
	Psychological capital			✓		✓					
	Future career anxiety			✓		✓					
	Depression			✓		✓					
	Anxiety			✓		✓					
	Mental health complaints			✓		✓					
	Physical health	✓									
	Financial strain	✓									
	Sociodemographics	✓									
	Treatment adherence					✓		✓			
	Treatment satisfaction					✓		✓			
	System usability					✓		✓			
	Employment status	✓						✓		✓	
	Job quality (if applicable)							✓		✓	

^a^t0: 2-3 weeks before iJobs; t1: randomization within 1 week before iJobs and pretest assessments for both groups; t2: posttest assessments within 1 week after iJobs for both groups; the control group starts iJobs; t3: follow-up screening 1 month after iJobs for the intervention group; posttest assessments for the control group at the end of iJobs; t4: follow-up screening 1 month after iJobs for the waiting list group.

^b^For a detailed description, see the *Outcomes* section.

### Outcomes

#### Primary Outcomes

##### Job-Search Intensity and Effort

We will use a contemporary version of Blau’s JSB scale, adapted to the Romanian context [16], to assess the frequency and intensity of participants’ job-search activities during the past 2 weeks. The scale consists of 16 items on a 5-point scale (1=never; 5=very frequent). Thus, 13 items measure job-search intensity (eg, “How often did you send your CV to potential employers?”), with a total score between 13 and 65, and 3 items measure job-search effort (eg, “You dedicated much of your time to job search.”), with a total score between 3 and 15. A higher score means a better outcome. JSBs will be measured at baseline, the postintervention time point, and follow-up.

##### Job-Search Quality

We will use the Job Search Quality scale [17] to assess the quality of the job-search process, with precisely 4 components: goal establishment and planning, preparation and alignment, emotion regulation and persistence, and learning and improvement. The scale has 20 items on a 5-point scale (1=not at all applicable to me; 5=fully applicable to me). Goal establishment (ie, job-search goals and planning are clear, specific, and systematic) is measured with 7 items (eg, “I was determined to find a job.”); the total score ranges between 7 and 35. Preparation and alignment (ie, preparation of job-search activities in alignment with what the organizations are looking for in their applicants) is measured with 5 items (eg, “I carefully studied the website of organizations where I was going to apply.”); the total score ranges between 5 and 25. Emotion regulation (ie, self-control facilitating persistence in the job-seeking process; eg, “I persisted in my job search, even though it was unpleasant at times.”) and learning (ie, reflection on the job search and ways to improve it; eg, “I thought about other ways to find a job beyond those I had already tried.”) are measured with 4 items; the total score ranges between 4 and 20. A higher score means a better outcome. Job-search quality will be calculated at baseline, the postintervention time point, and follow-up.

##### About JSSE

The JSSE [18] will be used to assess participants’ perception of their ability to gain employment. The scale has 20 items (eg, “I believe my job search will be successful”) on a 5-point scale (1=a little; 5=a great deal), with a total score between 20 and 100. A higher score means a better outcome. JSSE will be measured at baseline, the postintervention time point, and follow-up.

#### Secondary Outcomes Measures

##### Inoculation Against Setbacks

Inoculation against setbacks will be assessed using 2 items (eg, “Do you have an action plan for potential setbacks in the re-employment process?”), on a 5-point Likert scale (1=completely disagree; 5=completely agree), retrieved from Vuori and Vinokur [5], aiming to measure the participants’ ability to deal with setbacks in the job-seeking process. The minimum score is 5, and the maximum is 10. A higher score means a better outcome. Inoculation against setbacks will be measured at baseline and the postintervention time point.

##### Self-Esteem

Rosenberg’s [19] Self-Esteem Scale will be used to assess global self-worth by measuring both positive and negative feelings about the self. The scale has 10 items (eg, “I believe I have many qualities.”) on a 4-point scale (1=completely disagree; 4=completely agree). The minimum score is 10, and the maximum is 40. A higher score means a better outcome. Self-esteem will be measured at baseline and the postintervention time point.

##### About FCA

The FCA scale [20] will be used to assess participants’ anxiety regarding their future jobs. The scale has 5 items (eg, “I worry about future employment because of fierce competition in the job market.”) on a 5-point scale (1=completely disagree; 5=completely agree), with scores between 5 and 25. A higher score means a worse outcome. FCA will be measured at baseline and the postintervention time point.

##### Anxiety

The Generalized Anxiety Disorder–7 assessment [21] will be used to assess the severity of anxiety symptoms in the past 2 weeks, according to the *Diagnostic and Statistical Manual of Mental Disorders, Fifth Edition* criteria. The scale has 7 items (eg, “Over the past two weeks, how often you had trouble relaxing?”) on a 4-point scale (0=not at all; 3=nearly daily), with scores between 0 and 21. A higher score means a worse outcome. Anxiety will be measured at baseline and the postintervention time point.

##### Depression

Patient Health Questionnaire–9 [22] will be used to measure participants’ severity of depression symptoms in the past 2 weeks, according to *the Diagnostic and Statistical Manual of Mental Disorders, Fourth Edition* criteria. The scale has 9 items (eg, “Over the last two weeks, how often you had little interest or pleasure in doing things?”) on a 4-point scale (0=not at all; 3=nearly daily). The minimum score is 0, and the highest one is 27. A higher score means a worse outcome. Depression will be measured at baseline and the postintervention time point.

##### Mental Health Complaints

We will use the Mental Health Complaints Scale [23], a 5-item instrument (eg, “In the past two weeks, how often were you happy?”) with a 6-point scale (1=not at all; 6=all the time). The minimum score is 6 and the maximum is 30. A higher score means a worse outcome. Mental health complaints will be measured at baseline and the postintervention time point.

##### Psychological Capital

The Compound Psychological Capital Scale [24] will be used to measure participants’ psychological capital. The scale has 12 items (eg, “Right now, I see myself as being pretty successful.”) on a 6-point Likert scale (1=completely disagree; 6=completely agree), with a minimum score of 12 and a maximum of 72. A higher score means a better outcome. Psychological capital will be measured at baseline and the postintervention time point.

#### Other Measures

##### Physical Health

A short version of Ware’s Physical Health Complaints Scale [25] will be used to assess participants’ physical health. The scale has 4 items (eg, “I get sick easier than other people.”) on a 5-point scale (1=completely disagree; 5=completely agree). The minimum score is 5 and the maximum is 25. A higher score means a worse outcome. Physical health will be measured only at baseline.

##### Sociodemographics

At baseline, participants will fill in their age, gender, residential area, educational level, average monthly income, unemployment period, work experience, and targeted professional field.

##### Treatment Adherence Measures

We will assess the dropout rate, the number of completed modules, and the quality of the completed assignments. Two independent experts will rate the degree of completeness and depth of the answer for each assignment based on an a priori grid (eg, “The participant understood the assignments.”). Treatment adherence will be measured at the postintervention time point.

##### Satisfaction With the Intervention

Satisfaction with the intervention will be measured using 21 items. The scale consists of 5 items (eg, “My trainer is competent.”) retrieved from a questionnaire used for measuring the alliance between trainers and trainees in a face-to-face JOBS intervention [26], and 9 items (eg, “Overall, how satisfied are you with the program?”) and 7 open-ended questions retrieved from Richards et al [27] and previously used in questionnaires evaluating the satisfaction with interventions delivered on e-cbt [28], the platform we previously used to provide the program. Satisfaction with the intervention will be measured at postintervention time point.

##### Usability

The System Usability Scale [29] will be used to measure participants’ satisfaction with TalentLMS, the web-based platform we will use for program delivery. The scale has 10 items on a 5-point scale (eg, “I think I would like to use this platform frequently”; 1=completely disagree and 5=completely agree); the calculation formula suggested by Brooke [30] generates a score between 0 and 100. A higher score means a better outcome. Usability will be measured at the postintervention time point.

##### Employment Status

We will assess the self-reported employment status with a dichotomous question at follow-up (ie, “Do you currently have a paid job?”).

##### Job Quality

The job quality will be measured at follow-up only for the participants who found employment, with 4 questions (a dichotomous question and 3 questions on a 10-point Likert scale; eg, “How much do you like your current job?”; 1=not at all and 10=very much). Specifically, we will assess the satisfaction with the professional domain, overall tasks, and salary.

### Statistical Analysis

#### Power

The sample size estimation in GPower (Heinrich-Heine-Universität Düsseldorf) for a mixed factorial design aiming for a .80 statistical power is 132 participants. Based on our previous results from a feasibility and acceptability trial on iJobs, we can anticipate a possible dropout rate of about 36% (n=48). Thus, the final sample aimed for enrollment will be 180 eligible participants (see Figure 3 for the flowchart).

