### Trial Design

This study is a 2-arm randomized controlled trial (RCT) that will test the efficacy of a web-based adaptation of iJobs. Participants will be randomly assigned (1:1 allocation) to either the intervention group, which benefits from the iJobs program, or a waiting list control group that will also receive the iJobs intervention 2 weeks after the intervention group finishes it. The 2 independent groups (intervention vs waiting list control group) will be crossed with 3 measurement times (ie, baseline, the postintervention time point, and 1-month follow-up). Hence, the design will be a 2 (intervention vs control) × 3 (baseline, the postintervention time point, and 1-month follow-up) factorial design.

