## Results

The enrollment of study participants started in June 2023 and is expected to end in May 2024. Until September 2023, we organized 2 iJobs sessions. Out of the 130 randomized participants, we collected complete data (ie, pre- and postintervention) from 42 participants (*n*_intervention group_=14, *n*_control group_=28). The dropout rate from pretest to posttest in the intervention group was 44% (11/25) and 26% (10/38) in the waiting list control group (see Figure 3 for a flowchart). The data collection is expected to be completed by July 2024. The results are expected to be submitted for publication in the summer of 2024.

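### The dropout allowance is taken from the 132 required completers instead of from those enrolled: 180 enrolled at 36% dropout leaves about 115 completers, not 132

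*Protocol article*

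**What the plan says.** The Power section of the protocol article gives the G*Power result "for a mixed factorial design aiming for a .80 statistical power is 132 participants". It takes the expected dropout from the feasibility trial and goes on: "we can anticipate a possible dropout rate of about 36% (n=48). Thus, the final sample aimed for enrollment will be 180 eligible participants". Alpha, effect size and within-person correlation are not given there. For the enrolment count the section refers to Figure 3, which is not shown in the text available.

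The Data Analysis section plans an intention-to-treat linear mixed model, without imputation, on all eligible participants with pretest measures. The effect of interest is the group-by-time interaction from baseline to post-intervention.

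The Results section reports progress to September 2023: "Out of the 130 randomized participants, we collected complete data (ie, pre- and postintervention) from 42 participants". It also gives dropout from pretest to posttest as 11/25 (44%) in the intervention group and 10/38 (26%) in the control group.

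**The concern.** A dropout rate is a share of the people who enter, not of the people who remain. If 132 must remain and 36% of entrants leave, entrants number 132 divided by 0.64. The section multiplies 132 by 1.36 instead. Its two descriptions of the loss, 36% and 48 people, therefore cannot both be true of 180 enrolled.

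The enrolment target and the .80 power are figures that readers will rely on when they judge the result. As written, the target does not deliver the number said to be needed under the plan's own dropout assumption. The section also leaves open what 180 counts, and the progress figures show that this matters: many of those randomised do not appear in the pretest denominators.

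**Working it through.** **Inputs.** From the Power section: 132 required, power .80, dropout 36% (48 people), target 180. From Trial Design: 1:1 allocation. From Results: 130 randomised, 42 with pre and post data (14 and 28), dropout 11/25 and 10/38. Assumed here because not stated: two-sided alpha 0.05, and the effect size that gives exactly 80% power at 132.

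**1. Reproducing the plan's figures.**
- 0.36 × 132 = 47.5, rounded to 48.
- 132 + 48 = 180 (equivalently 132 × 1.36 = 179.5).

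Both stated figures come out. Dividing by 0.64 does not give 180.

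**2. What 180 delivers.**
- 180 × (1 − 0.36) = 115.2, about 115 completers; 132 − 115 = 17 short.
- 48/180 = 26.7%, the largest dropout at which 180 still leaves 132.
- 132/0.64 = 206.25, so 207 enrolled, or 208 for equal arms: 27 or 28 more than 180.

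**3. Power on completers only.** The noncentrality is set to give 80% at 132 and scaled to 115.

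| Method | Power at N = 115 |
|---|---|
| Normal approximation, two-sided 0.05 | 74.4% |
| F test, 1 numerator df (two time points) | 74.3% |
| F test, 2 numerator df (three time points) | 73.9% |
| Normal approximation, one-sided 0.05 | 75.0% |

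The figure hardly depends on the unstated inputs.

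**4. Power under the planned model.** The mixed model keeps participants who have only a pretest. With 90 per arm at pretest, 90 × 0.64 = 57.6 per arm at posttest, equal variances and within-person correlation r, the generalised least-squares variance of the interaction equals that of a trial of complete pairs with

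effective N per arm = 2 / [(1 + r)/57.6 + (1 − r)/90].

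| r | Effective N, both arms | Power (normal approximation) |
|---|---|---|
| 0.3 | 131.8 | 79.9% |
| 0.5 | 126.6 | 78.3% |
| 0.7 | 121.8 | 76.8% |

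For r = 0.5: 2 / (1.5/57.6 + 0.5/90) = 63.3 per arm, 126.6 in total. These figures assume that dropout is ignorable given the pretest.

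**5. What 180 counts.**
- *Pretest completers.* Observed dropout is (11 + 10)/(25 + 38) = 21/63 = 33.3%, close to the planned 36%. Then 180 × 2/3 = 120 completers. With 90 per arm and the arm-specific rates, the planned model gives about 76.5% to 79.8% power for r = 0.7 to 0.3.
- *Randomised participants.* 42/130 = 32.3%, and 180 × 0.323 = about 58 completers. Completer-only power, by the F tests in step 3, would be about 43% to 45%.

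Of the 130 randomised, 130 − 63 = 67 lie outside the pretest-to-posttest denominators.

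**The case against.** The strongest reply concerns the size, not the slip. The planned analysis is not a completer analysis. Pretest-only participants sharpen the baseline means, and at r = 0.5 they recover about 11 of the 17 missing completers (126.6 against 115.2). Under the planned model the loss is roughly 0 to 3 percentage points. This stands. A reader might infer that the trial's power is 74%, but that figure holds only for a completer-only calculation and needs that label.

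A second stronger reading is that the trial's own data are worse than planned and that power is far below 80%. The documents do not support this as it stands. The comparison in kind with the planned rate is dropout from pretest to posttest, which is 33%, slightly below 36%. The figures of 58 completers and 43% to 45% power follow only if 180 means randomised participants. The text does not settle that. The Procedure section says that eligible participants are randomised, which favours that reading. Against it, 130 had been randomised by September 2023, while enrolment was expected to run to May 2024 and further sessions were foreseen. The progress figures also come from two sessions only and may change.

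It may be added that the article openly reports the dropout and calls it a concern, and that allocation and analysis are unaffected. That is so, but it does not correct the paragraph. Nor does the word about: retaining 132 of 180 needs dropout of 26.7% or less, not 36%. And this is no omission of a condensed article, since rate, count and target are all printed and do not agree.

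**Conclusion.** The enrolment target is wrong as derived. This follows from the section's own four numbers, and nothing elsewhere in the text corrects it. At 36% dropout, 180 enrolled gives about 115 completers, 17 fewer than the number to which the .80 power is attached.

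The consequence for power is modest under the planned analysis: about 77% to 80% for r from 0.7 to 0.3 with ignorable dropout, against about 74% if only completers count. Both rest on two-sided alpha 0.05 and on the effect that gives 80% at 132. The 132 itself cannot be checked, because its inputs are not stated.

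The larger uncertainty is what 180 counts. If it counts pretest completers, the dropout reported so far leaves the position close to the plan. If it counts randomised participants, the shortfall is severe. The documents do not decide between the two, so neither should be asserted.

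**What to change.** Rewrite the dropout sentence in the Power section:

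- State that 180 enrolled at 36% dropout is expected to yield about 115 completers.
- Restate the power with its label: about 74% on completers only, or about 77% to 80% under the planned mixed model, giving the assumed correlation and the ignorable-dropout assumption. The authors should recompute this from their own G*Power inputs.
- Note that 132 completers correspond to 207 enrolled, or 208 for equal arms.
- Say whether 180 counts randomised participants or pretest completers. If pretest completers, cite the observed 33% and about 120 expected completers. If randomised, give about 58 expected completers at the observed 42/130 and restate the power accordingly.

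The cost is a few sentences and a less favourable figure. If the power is restated, no extra participants are needed. If 132 completers are to be kept, the target rises by 27 or 28.

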**Figure 3 figure3:**
[figure not shown]
CONSORT flow diagram with the estimated number of participants aimed by the end of data collection and the current status of enrolled participants. CONSORT: Consolidated Standards of Reporting Trials.

#### Data Analysis

We will use data from all the participants eligible for this study who completed the pretest measures. The data will be analyzed using the intent-to-treat framework with linear mixed model procedures. Intention-to-treat is based on the principle “once randomized, always analyzed.” It is a pragmatic approach to avoid bias in estimating the effect of treatment assignment in RCTs. We will use the linear mixed model approach without ad hoc imputations because it is more powerful than other options for studies with a high percentage of missing data [31].

For all the outcomes, time (baseline vs the postintervention time point) will be set as the within-group factor, and trial condition (intervention vs waiting list control group) will be used as the between-groups factor. We will analyze these 2 variables together with the entire set of outcomes (baseline vs postintervention comparison for the primary and secondary outcomes) to estimate the intervention’s effect size. Baseline to 1-month follow-up comparisons will be made to test how much the primary outcomes are preserved in time. We will also conduct separate analyses for each outcome with group, time, and group-by-time interaction as fixed effects and a random intercept for subjects with an identity covariance structure. The group-by-time interactions express the mean outcome change between the 2 trial groups from baseline to posttreatment.

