**Introductive module**
Participants will watch a short video explaining the platform’s main features (eg, how to complete exercises during the program and send messages to the counselors). At the end of the module, the participants must complete a questionnaire (eg, the pretest measures for the intervention group) to be enrolled in the intervention.

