**Figure 2 figure2:**
[figure not shown]
Study design and procedure overview. t0: 2-3 weeks before iJobs; t1: randomization within 1 week before iJobs and pretest assessments for both groups; t2: posttest assessments within 1 week after iJobs for both groups; the control group starts now iJobs; t3: follow-up screening 1 month after iJobs for the intervention group; posttest assessments for the control group at the end of iJobs; t4: follow-up screening 1 month after iJobs for the waiting list group.

The participants from the intervention group will receive an email with the iJobs calendar and brief instructions. Afterward, they will receive an email with the platform login information. The username will be a random combination of digits (eg, IJ105) to ensure participants’ anonymity during the program. The account password is generated automatically by the platform. Once participants access their accounts, an introductive module containing the baseline measures questionnaire will be available on the platform. Meanwhile, the waiting list control group participants will receive an email with the iJobs period and a link to the baseline questionnaire.

On the iJobs’ platform, each module will be available for completion for 27 hours. After participants receive personalized written feedback on the platform from the team of counselors involved in the program, the following module will become automatically available for completion. After the last module, the posttest questionnaires will be available on the platform for 48 hours.

Further, 2 weeks after the intervention group finishes iJobs, the control group will start the intervention and go through the abovementioned steps. The questionnaire from the introductive module is the posttest measure for the control group.

Additionally, 1 month after the intervention, the participants who complete the posttest measures will be contacted to complete a brief questionnaire that evaluates their employment status and JSBs.

An overview of this study’s period is presented in Table 1.

**Table 1 table1:** Study timeline. Time points and outcome assessments for the intervention group and waiting list group from enrollment to follow-up.

			Time point^a^								
			Enrollment (t0)		Randomization and pretest measurement (t1)		Posttest measurement (t2)		Follow-up intervention group (t3)		Follow-up control group (t4)
Enrollment			✓								
Eligibility screen			✓								
Informed consent			✓								
Randomization					✓						

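### The analysis is called intention-to-treat but is limited to people who completed a pretest taken after allocation; on the interim figures this leaves out 67 of 130 randomised (51.5%)

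*Protocol article*

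**What the plan says.** The Data Analysis section of the protocol article sets the analysis population: "We will use data from all the participants eligible for this study who completed the pretest measures". It continues: "The data will be analyzed using the intent-to-treat framework with linear mixed model procedures". It glosses intention-to-treat as "once randomized, always analyzed" and rules out ad hoc imputation.

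The timing of the pretest is fixed elsewhere:

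- The Figure 2 legend gives "t1: randomization within 1 week before iJobs and pretest assessments for both groups", with randomisation named first.
- The module overview (Introductive module) says that "the participants must complete a questionnaire (eg, the pretest measures for the intervention group) to be enrolled in the intervention".
- The Procedure section has the intervention arm receive a calendar and login details, then find the baseline questionnaire inside the platform. For the other arm, "the waiting list control group participants will receive an email with the iJobs period and a link to the baseline questionnaire".

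The Results section reports 130 randomised and 42 with complete pre and post data after two sessions (to September 2023). It adds: "The dropout rate from pretest to posttest in the intervention group was 44% (11/25) and 26% (10/38) in the waiting list control group".

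**The concern.** The route to the pretest depends on the arm, so allocation must already have been made when the pretest is taken. Completing it is therefore a post-randomisation event, and the effort it takes differs by arm. Intervention participants must log in to a learning platform and go through an introductory module. Controls follow a link. Limiting the analysis to completers is thus an exclusion that allocation can influence, and it does not fit the definition of intention-to-treat that the same section gives.

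At stake is the protection that randomisation offers. If the people who pass the pretest step differ between arms in something that also predicts how job-search intensity, effort, quality or self-efficacy changes, the group-by-time effect mixes the programme's effect with that selection. The mixed model does not remove the problem. It can deal with missing posttests, under missing at random, for people in the set, but it does not bring back people left out of the set for want of a pretest. A reader who sees the intention-to-treat label would assume a safeguard that the set does not provide.

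**Working it through.** **Inputs.** Randomised to date: 130 (Results). Pretest-to-posttest dropout: 11/25 intervention, 10/38 control (Results). Complete data: 42, being 14 and 28 (Results). Allocation ratio: 1:1 (Trial Design). Numbers randomised per arm: not in the text, and Figure 3 is not shown.

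**Step 1: reproduce the article's figures.** 11/25 = 44.0% and 10/38 = 26.3%. Completers: 25 − 11 = 14 and 38 − 10 = 28; 14 + 28 = 42. All agree with the article, so 25 and 38 are the numbers with a pretest in each arm.

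**Step 2: size of the exclusion.** With a pretest: 25 + 38 = 63, and 63/130 = 48.5%. Excluded between randomisation and the analysis set: 130 − 63 = 67, and 67/130 = 51.5%. This needs no assumption about the split.

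**Step 3: loss by arm over a range of splits.** With *a* randomised to intervention, the loss is (*a* − 25)/*a* in that arm and (130 − *a* − 38)/(130 − *a*) in control.

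| Assumed split (intervention:control) | Loss, intervention | Loss, control | Fisher p |
|---|---|---|---|
| 60:70 | 35/60 = 58.3% | 32/70 = 45.7% | 0.16 |
| 63:67 | 38/63 = 60.3% | 29/67 = 43.3% | 0.056 |
| 65:65 | 40/65 = 61.5% | 27/65 = 41.5% | 0.035 |
| 67:63 | 42/67 = 62.7% | 25/63 = 39.7% | 0.014 |
| 70:60 | 45/70 = 64.3% | 22/60 = 36.7% | 0.003 |

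The loss rates would be equal at *a* = 130 × 25/63 = 51.6, a split near 52:78. Under simple 1:1 randomisation, a split that uneven or more so has a two-sided binomial probability of 0.03. The direction (more loss in the intervention arm) therefore holds for any split reasonably close to 1:1. The strength of the evidence for it depends on numbers that the text does not give.

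**Step 4: what the selection does to the planned contrast.** The planned model has group, time and group-by-time as fixed effects, and the interaction is the treatment effect. Suppose a trait drives pretest completion and differs between the retained arms. If it shifts baseline and posttest by the same amount, it goes into the group term and cancels from the interaction. If it predicts change from baseline to posttest, it remains in the interaction as bias. The documents give no relation between pretest completion and change, so neither size nor sign can be computed.

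**The case against.** The strongest reply accepts the inconsistency and disputes its consequences. Four parts of it stand.

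- **Size and direction of bias.** A reader might infer a bias in favour of the intervention. At 65:65, entry to the set is 25/65 = 38% versus 38/65 = 58%. If entry selected on a standard normal motivation trait, the retained arms would differ by about 0.33 SD on it; a trait-outcome correlation of 0.1 to 0.5 would then give 0.03 to 0.16 SD. That calculation concerns posttest levels, not the planned group-by-time contrast. The sign is open too, since a more motivated arm could have less room to improve.
- **Unequal loss.** A reader might take differential loss as shown. Only the retained counts, 25 and 38, are known. The rates rest on an assumed split, and the figures are interim.
- **Knowledge of arm.** The emails make it likely that participants know their arm when they answer the pretest, but no section says that they are told.
- **An easy repair of past sessions.** Admitting anyone with a pretest or a posttest looks attractive. On the described procedure, however, posttest-only participants can arise only among controls, whose posttest is the introductory-module questionnaire when they start iJobs. In the intervention arm the pretest gates the programme and the posttest follows the last module. The rule would add people to one arm only. Nor can the t0 variables in Table 1 (physical health, financial strain, sociodemographics, employment status) stand in for missing outcome baselines, as none is an outcome scale.

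It can also be said that the article states its set openly and lists high dropout as a limitation. That is fair, but it does not reconcile the set with the label, and the Limitations section does not mention exclusion before the pretest.

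**Conclusion.** The point holds. By the article's own definition the planned analysis is not intention-to-treat: it is an analysis of pretest completers, selected after allocation by a different route in each arm. On the interim figures it leaves out 67 of 130 randomised (51.5%). That number is firm for the two sessions reported; the final share may differ. Higher loss in the intervention arm is probable given 1:1 allocation but is not established, because the numbers randomised per arm are not in the text. The selection can bias the group-by-time effect if what drives pretest completion also predicts change. How large that bias is, and which arm it favours, cannot be said from the documents.

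**What to change.** **Remaining sessions.** Collect the pretest from everyone by the same link before allocation is generated or disclosed. Place it as close to the start of iJobs as feasible: t0 lies 2 to 3 weeks before the programme, while the job-search behaviour, anxiety and depression scales ask about the past 2 weeks. Randomise only those who complete it, and analyse all who are randomised.

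**Sessions already run.**

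1. Call the set a modified (pretest-completer) set and drop the intention-to-treat label for it.
2. Report the numbers randomised and lost before the pretest in each arm, and compare t0 characteristics of included and excluded participants by arm. First confirm that these variables exist for everyone randomised: the measure descriptions place physical health and sociodemographics at baseline, whereas Table 1 places them at enrolment.
3. Add a sensitivity analysis on all randomised under stated missing-data assumptions, for example multiple imputation using the t0 variables, with departures from missing at random.

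**Cost.** The step before randomisation becomes longer, so some people will leave there, where their leaving cannot depend on allocation. The trial will contain two baseline procedures; adjust for or stratify by session. With 130 randomised by September 2023 against an enrolment target of 180, the reordering may reach only a minority of participants, and none if enrolment has closed. The relabelling, reporting and sensitivity analysis are needed either way and require no new data collection.
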